### Recruitment {15}

Local workers will be recruited from the trial village to enhance community engagement and study participation. Community sensitization procedures will include meetings with village leaders and inhabitants to introduce the study and each of its components.

#### Assignment of interventions: allocation

##### Sequence generation {16a}

The unit of randomization for the intervention and control will be a village cluster. For baseline, recruitment of participants for enrollment will be based on random HH selection following census and mapping of the study area. The study statistician will analyze baseline data to inform potential stratification criteria, i.e., baseline malaria incidence levels and/or adult entomological endpoints. Following stratification (as needed), allocation of individual villages to trial arms will be conducted using randomization. One of the eligible randomization allocations will be selected at a public ceremony in the presence of community leaders.

##### Concealment mechanism {16b}

Cluster allocation was randomly conducted using a lottery mechanism whereby pieces of paper will be marked ET and Control, placed in a basket, mixed, and then a randomly selected child will be asked to draw from the marked papers. Each drawn paper must correspond to a given village, until they are all listed out. This event will be a public ceremony in the presence of community leaders and the Ministry of Health.

##### Implementation {16c}

The study statistician will use a random number generator to generate the allocation sequence and assign clusters to treatment or control arms. Trained study staff will enroll participants to study clusters.

### Assignment of interventions: blinding

#### Who will be blinded {17a}

Given the nature of the intervention, it is impossible to conduct this study in a fully blinded manner but those parts of the data collection that can be blinded will be. Observer bias will be reduced where feasible. All laboratory work will be blinded. Mosquito collector bias will be reduced by using standard CDC light traps which do not rely on the ability of the fieldworker to collect specimens. Trap catches will not be examined and analyzed by those who collected them but by different technicians who will not know the trap location. We will use codes to identify any clinical samples. Electronic records will not carry the name of the research participants, only an alphanumeric code. Primary analysis by the project statistician will be conducted on blinded data (e.g., arms designated as treatment A and B or something similar).

#### Procedure for unblinding if needed {17b}

Datasets will only be unblinded once they have been locked.

### Data collection and management

#### Plans for assessment and collection of outcomes {18a}

##### Pre-trial

The pre-trial “ramp up phase” will be used to recruit and train local staff, and obtain ethical approval for the trial. During ramp up, forty candidate villages will be identified based on size (100–300 households) and proximity to Bouaké, Côte d’Ivoire, i.e., within a 50-km radius of Béoumi town in the Béoumi district of the Gbêkê region. We will select 34 of the 40 candidate villages based on ET suitability (no/small wall gaps, solid roof, no/small open eaves) and indications of participatory willingness based on meetings with the community leaders.

In each of the 34 trial villages, project personnel will meet with the authorities in each community (“chef du village”) to obtain permission to talk to the village residents about the trial. Village outreach will begin with town hall meetings to explain the trial and the possibility of a village being assigned to the treatment or the control arm, to outline all trial activities that will take place in the villages, and to answer any questions from the audience. A few days after the town hall meeting, the chef du village will be contacted to find out whether the community agrees to participate in the trial.

During ramp-up, a Population Census will be conducted in all the villages. Householders will be asked for information about their households (#, age, gender of family members in their HH) and given a new bed net if they have fewer than 2 per HH so that universal coverage is guaranteed in both trial arms. HH owners will be asked a short series of questions regarding their use of vector control tools, the availability of health care in the village, and markers of socio-economic status (house quality and availability of goods). For each HH, we will record the number of structures/dwellings, their construction (wall type, roof type, open eaves, wall gaps), number of windows, and number of doors. Following the local customs and local health ministry procedures in Côte d’Ivoire, each household (which typically does not have addresses) will be assigned a letter-number code that will be written in chalk on the door-jam of the house. During these activities, every eligible child in the village (between the ages of 6 months and 8 years old) will be assigned a unique identifier and their parents given a card with that unique identifier.

Community health workers will receive refresher training from a clinician before the onset of the trial baseline period.

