## Objectives {7}

### Main research question

This study intends to test whether ETs protect people against mosquitoes (entomological endpoints) and malaria (epidemiological endpoints) in an area where malaria transmission is driven by insecticide-resistant *Anopheles gambiae* mosquitoes.

The primary study objective is to assess whether ETs reduce the number of malaria infections and clinical malaria, defined by active case detection, in children between 6 months and 10 years of age, compared to children living in communities without ETs, in an area where there is universal coverage of LLINs (1 LLIN for every 2 people) and pyrethroid resistance is high.

Secondary objectives include:(i)To determine how ETs impact the rate of anemia (moderate anemia defined as 7–9.9 g/dL hemoglobin; severe anemia as < 7 g/dL hemoglobin)(ii)To assess how ETs impact Entomological Inoculation Rates (EIR) computed as the product of the anopheline vector density and the sporozoite rate, compared with LLINs alone(iii)To assess the cost-effectiveness of the ETs intervention(iv)To assess the user acceptance of the ETs intervention

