## Trial design {8}

The trial design is a 2-armed cluster randomized control trial (cRCT) with 17 clusters (villages) per arm for evaluating the protective efficacy of the SR intervention. Clusters are the unit of replication in this design, and they will be randomly allocated to one of the two arms. Both the replication and randomization in our design are essential to distinguish the effect of ETs from other village-level variation in malaria incidence.

Villages that have not participated in the previous SET cRCT, and villages that received standard pyrethroid-only LLINs (Permanet 2.0) from the National Malaria Control Program (NMCP) distribution campaign in May 2021 will be enrolled. We will exclude villages being treated by IRS and/or new generation bed net campaigns.

The control arm of this cRCT will include 17 villages with universal coverage of LLINs (defined as 1 LLIN for every 2 people) and no ETs. The 17 villages in the treatment arm will receive universal coverage of LLINs plus ETs. For those households assessed to not have met thresholds of universal coverage, topping up of LLINs will be conducted as needed.

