#### Relevant concomitant care permitted or prohibited during the trial {11d}

While the standard-of-care for clinical management of malaria and vector control interventions (e.g., LLINs, IRS) will not be withheld in either the study arm, these interventions will be monitored and recorded throughout the trial. At baseline, children enrolled into the cohorts will be provided a 3-day course of standard, first-line antimalarials (Coartem® or ASAQ Winthrop®, both Artemisinin combination therapies (ACTs) recommended by the NMCP in Côte d’Ivoire) to clear any malaria parasite infections as well as a new LLIN. In addition, subjects will be provided treatment for malaria infection throughout the follow-up period. Lastly, participants will be encouraged to continue LLIN use and not instructed to avoid alternative vector control tools (e.g., coils, topicals, aerosol sprays, repellents) which will allow for an estimation of the ET effect assuming all other measures are still occurring for malaria prevention, essentially providing insight on an additive benefit above that provided by currently recommended WHO malaria preventive measures.

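### The census bed-net rule, set at two nets per household, contradicts the protocol's own definition of universal coverage (one LLIN per two people) and its separate top-up commitment

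*Protocol article*

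**What the plan says.** Universal net coverage is defined in two places. Objectives {7} places the primary comparison "in an area where there is universal coverage of LLINs (1 LLIN for every 2 people) and pyrethroid resistance is high". Trial design {8} describes the control arm as "17 villages with universal coverage of LLINs (defined as 1 LLIN for every 2 people) and no ETs", and adds: "The 17 villages in the treatment arm will receive universal coverage of LLINs plus ETs".

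The document then gives two rules for reaching that state.

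- Trial design {8} ties the rule to the coverage threshold: "For those households assessed to not have met thresholds of universal coverage, topping up of LLINs will be conducted as needed".
- Plans for assessment and collection of outcomes {18a}, Pre-trial, ties it to a fixed count. Householders are "given a new bed net if they have fewer than 2 per HH so that universal coverage is guaranteed in both trial arms". The same paragraph says the census records the number of family members in each household.

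Two other places bear on nets. Under Relevant concomitant care {11d}, cohort children receive antimalarials at baseline "to clear any malaria parasite infections as well as a new LLIN". The schedule under Participant timeline {13} puts the census in the pre-trial period and lists LLIN distribution separately in the baseline period, without stating a rule for it.

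**The concern.** The definition scales with the number of people in the household; the census trigger does not. A fixed count of two can agree with one net per two people only over a narrow range of household sizes, yet the census text presents it as sufficient for every household in both arms. Field staff who follow that text would record a large household with two nets as covered. Staff who follow Trial design {8} would top it up.

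The stake is interpretation. The trial is meant to show what ETs add to standard control, with universal LLIN coverage as the stated background, and the results go to the WHO Vector Control Advisory Group. If larger households stay below one net per two people, the estimate describes ETs on top of partial coverage while the objective and the arm descriptions say otherwise.

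**Working it through.** **Inputs.** Definition: one LLIN per two people (Objectives {7}; Trial design {8}). Census trigger: fewer than two nets (Pre-trial). Cohort net: one new LLIN per enrolled child (Relevant concomitant care {11d}). Cohort: 55 children from 55 different households per cluster (Sample size {14}). Village size: 100 to 300 households (Eligibility criteria {10}). Household size and nets already held: not given. I count every net as an LLIN and treat the cohort child's net as additional.

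**Formula.** Nets needed by a household of n people = n/2, rounded up. Compare this with the nets held after the census rule.

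**Generous reading** (households below two are brought up to two):

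| People | Nets needed | People per net with 2 nets | 2 nets enough? | 2 nets + cohort net enough? |
|---|---|---|---|---|
| 1–2 | 1 | 0.5–1.0 | yes | yes |
| 3–4 | 2 | 1.5–2.0 | yes | yes |
| 5–6 | 3 | 2.5–3.0 | no | yes |
| 7–8 | 4 | 3.5–4.0 | no | no |
| 9–10 | 5 | 4.5–5.0 | no | no |

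A household of five or more that starts with zero, one or two nets therefore ends the census step below the definition.

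**Literal reading** (one net is given when fewer than two are held). A household of three or four with no net ends with one net, that is three to four people per net, and also falls short. The shortfall in households of five or more remains.

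**The guarantee.** The plan's claim that the rule ensures universal coverage is reproduced under neither reading. The trigger of two equals the number needed only at sizes three and four. In households of one or two it can supply a net beyond the definition, which does no harm.

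**Reach of the cohort net.** Cohort households are 55/300 = 18% to 55/100 = 55% of a village. So 45% to 82% of households get no such net, although coverage is stated for villages.

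**How many households?** This cannot be computed. As an illustration only, assume household size is one plus a Poisson variable. The share with more than four people is then 14%, 35%, 57%, 73% and 92% at mean sizes 3, 4, 5, 6 and 8. The share with more than six is 2%, 8%, 21%, 38% and 70%. These figures show which households could be short under the census rule alone. They are not estimates of shortfall, because they ignore nets already held and the other top-up rule.

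**The case against.** The strongest reply is that the census sentence is not the whole net plan. Trial design {8} promises a top-up that would meet the definition, the schedule shows a later LLIN distribution step, and eligible villages already received campaign nets. The census text says a net is given if a household has fewer than two; it does not say only if. The two rules could therefore run in sequence, a minimum at census and a threshold-based top-up afterwards. The primary outcome is also measured in cohort children, who each receive a new net.

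Much of this stands. A reader might infer that the trial will fail to deliver universal coverage; the documents do not establish that, because applying the Trial design rule would deliver it. A reader might also infer that protective efficacy is biased. That is not supported either: the census rule does not depend on arm, and the Baseline section places randomization after the census. No sample size, power or error-rate figure depends on the point.

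The reply does not rescue the sentence itself. It gives a specific number and a specific guarantee, and the guarantee is arithmetically false against the protocol's own definition. Nothing in the document says that the census rule is only a first step or which rule governs. Because this is a stated rule rather than an omitted detail, the condensed form of a journal article does not explain it.

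**Conclusion.** The point holds as an internal inconsistency. The census rule contradicts the definition of universal coverage and differs from the top-up commitment in Trial design {8}. Two nets suffice up to four people, and three nets, where a cohort net is added to two, suffice up to six. Beyond those sizes the guarantee is false for a household that holds no more than those nets. This rests only on the stated definition and on counting each net as an LLIN.

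The number of households left short is unknown, and the illustrative shares above should not be read as its size. The consequence is limited to the description of the background on which the benefit of ETs is estimated; the comparison between arms is not itself distorted. The inconsistency should be corrected, but it does not threaten the validity of the primary test.

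**What to change.** Reconcile the Pre-trial census paragraph with Objectives {7} and Trial design {8}, so that the protocol carries one top-up rule. That rule should use the protocol's own definition of coverage and the household member count the census already collects, and it should apply identically in both arms at the LLIN distribution or top-up step. Delete the statement that a threshold of two nets guarantees universal coverage.

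The schedule dates the census to January–February 2023, and Trial status reports the baseline survey complete by June 22, 2023, so rewording the census procedure alone may come too late. If the census rule has already been applied, report the nets per person actually achieved in each arm instead of asserting universal coverage. Relevant concomitant care {11d} already plans to record vector control measures, including LLINs, throughout the trial.

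The cost is a short text change, a coverage table, and some extra nets for larger households, which Trial design {8} already commits to supplying.

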##### Follow-up

At the start of the clinical follow-up period, the clean ET netting inserts will be replaced with the deltamethrin-treated ET inserts in all treatment clusters. This is estimated to take 2–3 weeks’ time.

Clinical follow-up will run for 2 years to cover two high transmission seasons (typically associated with the rains, May–October) and the remaining lower transmission periods.

**Epidemiological monitoring**

The incidence of malaria infection and clinical malaria will be determined by active case detection in febrile children in the study cohorts. Clinical monitoring and treatment will be performed by trained nurses from the Institut Pierre Richet, who will collaborate with the community health workers present in the trial villages. On the first visit, in the trial baseline period, parasite prevalence will be measured in all cohort children by RDT (SD Bioline Malaria Ag P.f/Pan; Standard Diagnostics; Seoul, South Korea). Immediately following this initial blood sampling, every child will be treated with a 3-day course of standard, first-line antimalarials (Coartem® or ASAQ Winthrop®, both ACTs recommended by the NMCP in Côte d’Ivoire) to clear any malaria parasite infections.

Children enrolled in the active detection cohort will be visited every 2 weeks during the peak malaria transmission season (May–October) and monthly during the rest of the year when transmission rates are low (November–April). At each visit, the clinical team will record the axillary temperature of each child. If the child is febrile or has a history of fever in the past 48 h or the parents report that their child was sick, the child receives a physical examination and a record will be made of symptoms. A finger prick blood sample will be taken from all febrile children. RDTs will be used to detect *Plasmodium* infection.

Children who are RDT-positive and are diagnosed with uncomplicated malaria by the study nurse will be treated immediately with first-line antimalarials for 3 days. This is the standard procedure for diagnosing and treating malaria in Côte d’Ivoire. Because it is a malaria-endemic region, only symptomatic children are typically treated. ACT treatment for malaria will be provided free of charge through the NMCP system. The community health worker who normally provides diagnostic and treatment in the village will be responsible for monitoring the child until he or she is cured. If the child exhibits any symptoms of severe illness, he or she will be sent immediately to the closest health clinic for treatment. Children who have been treated for malaria will be considered not at risk for 2 weeks following treatment and there will be no data collection for these individuals during this time. Nurses and community health workers will capture history of travel away from the household to flag any cases that might be a result of infection while traveling outside the village.

Clinical malaria incidence will also be monitored continuously by passive case detection using the existing clinical system: Community Health Workers and local health facilities. Any enrolled child between 6 months and 10 years old will be counted whenever they are brought to a community health worker or local health clinic with a body temperature of ≥ 37.5 °C. These data are planned to be provided weekly to ET Trial personnel.

Twice a year (at the beginning and end of the peak transmission season), all cohort children of 5 years of age or younger will have a blood sample taken for immediate measurement of anemia. Blood samples will be checked for hemoglobin levels using a spectrophotometer (Hemocue Hb diagnostic system).

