### Outcomes {12}

The primary outcome measure is the incidence rate of malaria infection as measured by active infection and clinical malaria case detection in cohorts of 55 children (between 6 months and 10 years old) per cluster, 17 clusters per arm on a biweekly basis in peak transmission season and monthly basis in low transmission season. [Time Frame: 24 months].

Secondary outcome measures include:Clinical malaria incidence measured in children between 6 months and 10 years old living in the study cohorts using passive case detection via the existing community health workers and health centers. [Time Frame: 24 months]Malaria parasitemia measured in children between 6 months and 10 years old in the cohorts of 55 children. [Time Frame: 24 months]Prevalence of moderate (defined as 7–9.9 g/dL hemoglobin) to severe anemia (< 7 g/dL hemoglobin) measured in children under 5 years of age in the cohorts of 55 children four times: at the start and end of the rainy season (April and November respectively) of Year 1 and Year 2. [Time Frame: 24 months]Mean numbers of female malaria mosquitoes (*An. gambiae s.l., Anopheles funestus s.l.*) captured in study houses measured by CDC light traps in 20 clusters, 10 houses per cluster on a monthly basis. [Time Frame: 24 months]Malaria parasite sporozoite rate assessed in 10% of all anophelines captured by CDC light trap. [Time Frame: 24 months]Entomological inoculation rates measured in each study arm as the product of the anopheline vector density and sporozoite rate. [Time Frame: 24 months]

Other pre-specified outcome measures include:7.Cost modeling will assess the cost-effectiveness of EaveTubes compared to the previously applied Screening + EaveTubes intervention, and compared to other vector control interventions such as long-lasting insecticide nets and indoor residual spray. [Time Frame: 24 months]8.Assessments of willingness to participate and adoption of EaveTubes at the end of the study period through questionnaires and willing-to-pay surveys. [Time Frame: 24 months]

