### Statistical methods

#### Statistical methods for primary and secondary outcomes {20a}

The baseline characteristics of the enrolled subjects, households, and clusters will be summarized by treatment arm (control arm, LLIN and intervention arm, ET + LLIN). Specifically, we will examine subject age and gender at the individual level, wall type and roof type, house open eaves, number of windows, number of doors at the household levels, and cluster population and baseline prevalence rate at the cluster level.

In the following analysis that involves malaria incidence, a child will not be considered at risk for malaria for 2 weeks after any treatment for malaria.

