**Effect of ETs on malaria prevalence**

Malaria prevalence data will be collected at baseline and at the end of Year 1 and Year 2. A mixed-effects logistic regression as used in the anemia analysis above will be used to compare ETs and control on malaria prevalence over time, with the outcome anemia status being replaced malaria status (Y or N).

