#### Adverse event reporting and harms {22}

Safety oversight will be carried out by the TSC. Children of the study cohorts will have access to the current standard of care. Serious adverse events (SAEs), whether attributed or not to ETs or LLINs, will be recorded throughout the trial. The host institution medical expert ([name]) and his clinical team will be responsible for recording, reporting, and managing SAEs, including follow-up, in accordance with national guidelines. A summary table of all SAE will be provided at regular intervals to the TSC.

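### The bar on data collection for two weeks after malaria treatment has no stated limit and contradicts the anaemia survey, passive detection and SAE recording

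*Protocol article*

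**What the plan says.** The two-week window appears twice in the Protocol article, with different scope.

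- Epidemiological monitoring (field procedures): "Children who have been treated for malaria will be considered not at risk for 2 weeks following treatment and there will be no data collection". Nothing restricts this to malaria testing.
- Statistical methods {20a}: in analyses of malaria incidence, "a child will not be considered at risk for malaria for 2 weeks after any treatment for malaria". This is a person-time rule only.

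Other text presupposes that data keep coming from every child.

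- Epidemiological monitoring: twice a year "all cohort children of 5 years of age or younger will have a blood sample taken for immediate measurement of anemia", with no exception for recent treatment. Outcomes {12} places these surveys "at the start and end of the rainy season (April and November respectively) of Year 1 and Year 2".
- Epidemiological monitoring: passive detection through health workers and clinics is continuous, and a treated child is followed by the community health worker until cured.
- Effect of ETs on malaria prevalence: "Malaria prevalence data will be collected at baseline and at the end of Year 1 and Year 2".
- Adverse event reporting and harms {22}: "Serious adverse events (SAEs), whether attributed or not to ETs or LLINs, will be recorded throughout the trial".
- Missing data {20c}: missed visits are treated as ignorable when the reason is unrelated to the product or the outcome.

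**The concern.** The incidence analysis needs only the at-risk rule. The field text adds an instruction to collect nothing, and field teams work from the field text. A team that follows it literally would skip a child treated in the last 14 days at the haemoglobin survey and at the prevalence survey, and would record no adverse events in the fortnight after a malaria episode. That section itself foresees severe illness needing referral, and the protocol counts hospitalisation as an SAE.

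If ETs work, more control than ET children are inside the window on any survey day. Absence from the survey would then depend on recent malaria, which lies between the intervention and the outcome. The ignorability condition in {20c} does not cover this, and the covariates described for the anaemia model do not include recent treatment. If teams read the rule differently, missingness would also vary by village. A haemoglobin value not taken on the day cannot be recovered.

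**Working it through.** **The plan's own figure.** The documents give no figure for this point. As a check that the design inputs are read correctly, take 17 × 55 = 935 children per arm, 20% loss, a control rate of 1.5 per person-year, PE 35% (ET rate 0.65 × 1.5 = 0.975) and two years:

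935 × 0.8 × [(1 − e^(−3)) + (1 − e^(−1.95))] = 748 × (0.950 + 0.858) = 1352 first events, against 1315 stated, a difference of 2.8%. The inputs are read as the plan intends.

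**Share of children inside the window.** With rate r and w = 14/365.25 = 0.0383 years, the share on any day is f = rw/(1 + rw). The rate of 1.5 is from Sample size {14}; 2–3 per child-year is from Study setting {9}.

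| Control rate per person-year | Control | ET (rate × 0.65) | Gap (points) |
|---|---|---|---|
| 1.5 | 0.0575/1.0575 = 5.4% | 0.0374/1.0374 = 3.6% | 1.8 |
| 2.5 | 8.7% | 5.9% | 2.8 |
| 3 | 10.3% | 7.0% | 3.3 |

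At 1.5 this is about 51 against 34 of 935 children; the haemoglobin survey covers only those aged five or under, so its counts are smaller. The shares assume that every episode is treated as it occurs, so they are upper figures at each rate.

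**Effect on the anaemia odds ratio.** Assumptions not in the documents: anaemia of 10–30% in control children not recently treated, OR 0.70 among children not recently treated, and anaemia 1.5 to 3 times as common in recently treated children.

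Worked case at 1.5 per person-year, with 20% anaemia and a ratio of 2:
- ET children outside the window: odds 0.25 × 0.70 = 0.175, so 14.9%.
- Everyone included, control: 0.20 × (1 + 0.054) = 21.1%.
- Everyone included, ET: 0.149 × (1 + 0.036) = 15.4%.
- OR with everyone included: 0.683. OR after exclusion: 0.700. Ratio: 1.025.

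Over the assumed ranges:

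| Control rate | OR, everyone included | OR after exclusion | Shift towards 1 |
|---|---|---|---|
| 1.5 | 0.66–0.69 | 0.70 | about 1–6% |
| 2.5 | 0.64–0.69 | 0.70 | about 2–10% |

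If recently treated children are no more often anaemic than others, the shift is zero.

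**Effect on prevalence.** Assume 50% against 40% outside the window and 1.5 per person-year. The OR after exclusion is 0.667. With everyone included it is 0.70 if recently treated children test negative, and 0.66 if 90% of them stay RDT-positive. The bias can go either way.

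**The case against.** The strongest reply is that the narrower meaning is the intended one. The sentence opens with being not at risk, follows the text on case detection and treatment, and uses the same two weeks as the incidence rule. No section says that treated children are left out of a survey or of SAE recording, and several imply the opposite. SOPs are still to be developed and may settle it. This stands against any claim that removal is certain. It does not remove the contradiction, because the only field instruction printed is the unrestricted one.

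The second reply concerns timing. The anaemia surveys fall in April and November, when visits are monthly and transmission is low. A child treated at the previous active visit is then past 14 days, so mainly passively detected cases remain inside the window, apart from an early November survey following a late October visit. This stands, and the shares above are probably too high for anaemia. It carries over less well to prevalence. If Year 1 and Year 2 are follow-up years on the July 2023 to June 2025 timetable, those surveys fall around June, in the peak season with visits every two weeks.

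A reader might infer that the rule could erase the anaemia effect. That would require ETs to act on anaemia only through malaria treated in the last 14 days, which nothing in the documents supports. Even then, with assumed anaemia of 45% inside and 20% outside the window, the OR being lost is about 0.97 at 1.5 per person-year. If ETs also lower anaemia outside the window to an assumed 16%, exclusion moves the OR only from about 0.756 to 0.762.

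**Conclusion.** The contradiction is established from the text: an unlimited bar on data collection cannot stand beside a survey of all cohort children aged five or under, continuous passive detection and SAE recording throughout, and the incidence analysis does not need it. The statistical consequence is conditional on literal application. It would then produce missingness related to arm and outcome, of the size tabulated above, that the missing-data section does not cover.

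For anaemia, the shift towards no difference is modest and rests on recently treated children being more often anaemic, which the documents do not state. For prevalence, no direction can be claimed. For safety, the loss would be the fortnight after each treated episode. The primary endpoint is not affected, because those 14 days are outside person-time at risk under either reading. The documents do not support saying that children will in fact be removed, or that the anaemia comparison is seriously biased. The point is worth acting on because the remedy is cheap and missed survey measurements are lost for good.

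**What to change.** Reconcile the passages by replacing the final clause of the rule under Epidemiological monitoring. Suggested wording: these 14 days are removed from malaria person-time at risk, and malaria detections within them are not counted as new events; haemoglobin surveys, prevalence surveys and AE/SAE recording continue unchanged for all cohort children.

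Keep recently treated children in the anaemia and prevalence analyses, and record the date of last malaria treatment at each survey so that a sensitivity analysis is possible. Carry the same wording into the field SOP.

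Cost: one sentence and one recorded date. A few more children are measured at surveys that already take place. No new procedure is needed and treatment does not change.
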